### Sample size determination

Given the pilot nature of this trial, we will focus on the feasibility of the study and ensure that the exercise intervention runs smoothly, we will not calculate a sample size to determine the power in this study [20]. However, it is recommended that a minimum of 30 participants is required to achieve sufficient precision to enable sample size calculation for subsequent studies [21]. Therefore, we plan to recruit 40 participants, which will allow the completion of data collection from 30 subjects, with a 75% participant retention rate.

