#### Exercise intervention

The exercise intervention is an outpatient clinical rehabilitation program delivered one-on-one to individuals in a 30-min session and three times a week for 8 weeks in the hospital outpatient clinic. The 30-min CR procedure includes 5 min of warm-up exercise, 20 min of cycle ergometer (Ergoline GmbH, Germany) exercise with targeted intensity, and 5 min of cool-down exercise. The targeted intensity is set as the heart rate 1 min before AnT based on CPET. We expect that exercise parameters will improve gradually as individuals reach their targeted intensity more frequently with time over the 8 weeks. Participants are closely monitored using a heart rate monitoring device connected to the cycle ergometer and will be guided by the CR team, which consists of cardiologists, rehabilitation physicians, physiotherapists, nurses, and clinical research coordinators. The research coordinator will record the attendance of each participant and will ask the participant to come on the weekend to compensate for any missed sessions. In addition, the CR protocol can be extended to accommodate an intervening illness. Nevertheless, the participant is allowed to quit the program at any time if he/she wants to do so. Participants will be followed closely to ensure adherence. All CR providers are trained to follow the same protocol to ensure intervention fidelity. Participants in the control arm will receive telephone calls once a week to monitor their physical conditions and will be encouraged to take a walk at least 30 min at a time and three times a week during the 8-week study at home but not at the program center. The information for the control group will be recorded using activity tracking apps such as activity tracker bands, watches and smartphones so that the authors will know how active the control-arm participants are. The second CPET will be conducted after the 8-week CR program. Graduates will also be advised to take concomitant medications, continue engaging in appropriate exercise, eat a balanced diet, and quit smoking.

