### Data collection

Assessors are trained to collect trial data from the outpatient clinic and laboratory. The following data will be collected from all participants before and after the rehabilitation training as shown in the SPIRIT diagram (Fig. 2): the aerobic metabolism parameter (AnT), clinical indicators (blood pressure, heart rate, body mass index, smoking status, and comorbidities), laboratory indicators (total cholesterol, high-density lipids (HDL)-cholesterol, low-density lipids (LDL)-cholesterol, triacylglycerides, apolipoproteins, homocysteine, glucose, etc.), and blood samples for additional biomarkers (C-reactive protein, macrophage inflammatory protein-1α, pentraxin-3, monocyte chemotactic protein-1, interleukins, transforming growth factor-β, interferon-γ, brain natriuretic peptide, growth differentiation factor-15, vascular endothelial growth factor-B, myeloperoxidase, adiponectin, matrix metalloproteinase-1, 2, or 9, matrix metalloproteinases tissue inhibitor-1, phosphodiesterase-9A). Data will be collected at 3 months to assess the short-term prognosis and risk factors for cardiac adverse events after the CR program.

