### Data assessment

The objective of this pilot study is to test the feasibility of recruitment, retention, intervention, and collection of data on aerobic metabolism parameters and clinical and laboratory measurements at the same time. Mean changes in outcomes over time will be summarized graphically and descriptively within each group. These changes will be compared between groups and will be described with associated 95% confidence intervals to explore possible effects of the intervention, recognizing that this pilot trial is not powered to detect clinically meaningful effects. Feasibility parameters, such as recruitment rate and retention rate, will be analyzed to determine whether it is worth continuing to conduct a large-scale trial that builds from the current pilot trial. The key feasibility criteria include recruitment of 40 participants, attainment of a 75% participant retention rate, and measurement of all outcomes in 90% of all participants. These parameters will be assessed at the end of the pilot trial by a statistician who is not involved in the study.

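### With all 40 participants as denominator, the 90% outcome-completeness criterion (36 of 40) cannot be met at the planned and accepted 75% retention (30 of 40)

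*Protocol article*

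**What the plan says.** The Data assessment section of the protocol article sets out the feasibility criteria. "The key feasibility criteria include recruitment of 40 participants", followed by "attainment of a 75% participant retention rate, and measurement of all outcomes in 90% of all participants". The feasibility parameters "will be analyzed to determine whether it is worth continuing to conduct a large-scale trial", and a statistician from outside the study assesses them at the end of the pilot.

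The Sample size determination section takes 30 participants as the recommended minimum for planning a later trial. It sets recruitment at 40, "which will allow the completion of data collection from 30 subjects, with a 75% participant retention rate". Retention is there tied directly to completed data collection.

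Two other sections show that the outcomes depend on a visit after the programme. Data collection: "The following data will be collected from all participants before and after the rehabilitation training". Exercise intervention: "The second CPET will be conducted after the 8-week CR program".

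The article does not define retention further. It does not say whether the 90% refers to everyone recruited or only to those retained, although the wording points to everyone. It gives no rule for combining the criteria.

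**The concern.** A participant who leaves before the second exercise test and the second blood sample cannot have all outcomes measured. Complete outcomes can therefore never exceed retention. A completeness threshold of 90% of everyone is then a stricter retention threshold in disguise, and it sits beside a stated retention threshold of 75%.

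Feasibility is the primary outcome, and these thresholds inform the decision on a large trial. A pilot that lands exactly on its planning figure would meet one key criterion and miss another. The printed text gives the outside statistician no way to say what that combination means. The 75% figure also suggests a tolerance for loss that the third criterion does not allow.

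**Working it through.** **Inputs.** Recruitment 40, retention criterion 75% and completeness criterion 90% of all participants (Data assessment). Planned completers 30 (Sample size determination). Outcomes measured before and after the programme (Data collection; Exercise intervention).

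**Step 1: the plan's own figure.** 30 / (1 − 0.25) = 30 / 0.75 = 40. The recruitment target reproduces exactly, so the sample size arithmetic is sound.

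**Step 2: thresholds as counts, with all 40 as denominator.**
- Retention: 0.75 × 40 = 30.
- Completeness: 0.90 × 40 = 36.
- Shortfall at planned retention: 36 − 30 = 6 participants.

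**Step 3: which results meet which criterion**, taking every retained participant as complete:

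| Completers of 40 | Share | Retention ≥ 75% | Completeness ≥ 90% |
|---|---|---|---|
| 29 or fewer | ≤ 72.5% | missed | missed |
| 30 to 35 | 75% to 87.5% | met | missed |
| 36 to 40 | 90% to 100% | met | met |

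No row has completeness met and retention missed. The 75% floor therefore never decides whether both criteria are met.

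**Step 4: chance of reaching each count.** X is binomial with n = 40 and probability p, and P(X ≥ k) is the sum over j = k, …, 40 of C(40, j) p^j (1 − p)^(40 − j). Participants are assumed independent.

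| True retention p | P(X ≥ 30) | P(X ≥ 36) |
|---|---|---|
| 0.75 | 0.584 | 0.016 |
| 0.80 | 0.839 | 0.076 |
| 0.85 | 0.970 | 0.263 |
| 0.90 | 0.999 | 0.629 |
| 0.95 | 1.000 | 0.952 |

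At p = 0.75 the chance of landing on 30 to 35 completers is 0.584 − 0.016 = 0.568. If some retained participants lack an outcome, the chances in the last column fall.

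**Step 5: the alternative denominator.** If the 90% applied to retained participants only, 0.90 × 30 = 27 would suffice at 75% retention and the misalignment would disappear. But 27 of 40 is 67.5%, and 27 is below the 30 complete datasets that the sample size section treats as the minimum. To have 30 complete at 90% completeness takes 30 / 0.90 = 33.3 retained, so about 34 of 40 (85%). With whole-number rounding, 33 retained would just do, since 0.90 × 33 = 29.7 rounds up to 30.

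**Step 6: precision.** The exact 95% confidence interval for 30/40 is 0.588 to 0.873.

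**The case against.** **Contradiction.** A reader might infer that the thresholds contradict each other, so that any trial reaching its planned retention must fail. The documents do not support this. Both figures are minimums, and both can be met with 36 to 40 completers. Nor does the article say that missing one criterion means overall failure: one met and one missed is a result that a feasibility report can state.

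**Forecast.** The 75% is an allowance that secures 30 datasets, not a prediction. The 1.6% is therefore the chance at the lowest accepted retention, not the expected chance. This stands, and it is why the table gives a range.

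**Post hoc choice.** One might also infer that the reading of the criteria would be chosen once the data are known. The limitations paragraph of the Discussion refers to a pre-specified analysis plan applied by an uninvolved statistician. That plan is not shown and may settle the denominator and the combining rule, so the inference is unsupported.

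**Primary outcome.** The Outcome measurements section names only recruitment and retention rates as feasibility parameters. The 90% criterion appears only under Data assessment, so it is better called a key feasibility criterion than a component of the primary outcome.

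**Denominator.** The 90% could be meant for retained participants. The wording refers to all participants without restriction, so this reading needs a change of text. The reply that participants who leave might still be measured finds no support, because the sample size section equates retention with completed data collection.

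What remains is a mismatch between printed thresholds, not detail left to another document.

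**Conclusion.** The point holds as a misalignment. With all 40 as denominator, 90% completeness is out of reach at the retention that the protocol plans for and accepts: 30 against 36, a gap of six participants. Results from 30 to 35 completers split the two criteria, and the 75% floor is redundant. The chance of reaching 36 of 40 runs from 1.6% at 75% true retention to 63% at 90%.

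This rests on three assumptions: that the denominator is everyone recruited, as the sentence literally reads; that a participant who leaves has no post-programme outcomes, as the sample size section implies; and, for the probabilities, that participants are independent and every retained participant has all outcomes. It does not show that the trial must fail, and it leaves the sample size arithmetic untouched.

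**What to change.** Before outcome data are reviewed, choose one of two routes.

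- **(a) Retained participants as denominator.** Restate the third criterion as all pre- and post-programme outcomes measured in at least 90% of retained participants. Keep 30 participants with complete data as a separate floor; without it, 27 of 30 would pass below the protocol's own minimum. At 90% completeness this needs about 34 of 40 retained, so restate the 75% planning figure accordingly.
- **(b) All randomised as denominator.** If 90% of everyone is intended, raise the retention criterion to at least 90% and correct the 75% planning figure in the sample size section.

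Under either route, define retained as attending the second exercise test and blood draw, and state how the criteria combine. Report each rate with its 95% confidence interval (30/40 gives 59% to 87%).

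The cost is a few sentences, but they amend a success criterion in an ethics-approved trial with 13 patients already enrolled at submission. Route (a) also lowers the literal requirement of 36 complete participants. The amendment should therefore be dated, and should say that it was made without sight of outcome data.

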## Discussion

The benefits of CR are well-recognized in America and Europe and are widely recommended by the American Association of Cardiovascular and Pulmonary Rehabilitation and European Society of Cardiology as secondary prevention in patients with coronary disease [7, 22, 23]. However, the CR program is far underdeveloped and in China has thereby resulted in a high rate of recurrence of heart attacks and adverse cardiovascular events [24]. China faces an aging population with an increasing lifespan, which will result in a large proportion of people suffering from cardiovascular events in the near future. Therefore, increasing awareness of the benefits of CR, improving CR availability throughout China, and providing safe and effective CR programs for Chinese patients with CHD are extremely important.

To our knowledge, the present pilot trial is the first clinical study that comprehensively screens multiple blood biomarkers to explore the potential underlying molecular mechanisms and changes in cardiovascular function after aerobic exercise-based CR training. Results of this pilot study can be used to predict the feasibility and operational acceptability of a future large-scale pivotal trial that promotes the generalization of the CR program in China.

However, this pilot trial has several limitations. Given the large age range of subjects from 45 to 80 years and the relatively small sample size after allocation to subgroups (male and female), physiology and biomarker profiles can vary greatly. The second limitation is the disparate modes between the intervention (cycle ergometer) and control (walk) groups. Specifically, the intervention group receives cycle ergometer training for exercise safety and to prevent patients from falling during treadmill training whereas the control arm does not receive this training. Moreover, whereas all of the intervention participants will be monitored with a standardized heart rate monitor during each intervention session, activity in the control arm will not be monitored using the same tool and will instead be monitored by whatever tracking app the participant has available. As a consequence, the data quality may be of very low quality or missing in the control arm. The third limitation is that outcome assessment of metabolism and clinical indicators (blood pressure, heart rate etc.) is not blinded. As a consequence, the quantitative results of the trial may not be completely reliable as there could be different quality of assessments in the two groups of the trial. However, a statistician who is not involved in the study will be invited to assess the data according to a pre-specified analysis plan, and the groups will be labeled A and B, to ensure that the data are analyzed blind. In a future larger trial, procedures will be put in place to ensure blinding of outcome assessors to avoid bias. The feasibility measures are the focus of the current pilot study and these will not be subject to potential observer bias.

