### Randomization

Participants will be randomly allocated (1:1 ratio) to either the intervention or control group once screening assessments are completed and eligibility for the study is confirmed (Fig. 1). A research coordinator will generate the random allocation sequence, enroll participants, and assign participants to interventions. A stratified randomization scheme based on gender will be used. Microsoft Excel Formula Rand will be used to allocate patients to the intervention or control group. A random number between 0 and 1 will be generated for each patient; if the last digit is an even number the patient will be assigned to group A (intervention) and if the last digit is an odd number the patient will be assigned to group B (control) (Table 3). Forty participants will be allocated randomly to group A (intervention exercise group with targeted intensity, *n* = 20) or B (control group with leisure exercise, *n* = 20).

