**Fig. 1 Fig1:**
[figure not shown]
Study flow chart. Eligible participants with coronary heart disease (CHD) after percutaneous coronary intervention (PCI) will be randomly allocated to the intervention or control group. The exercise intervention is an outpatient clinical rehabilitation program with targeted intensity, which includes a 30-min session three times a week for 8 weeks. Participants in the control group will be prescribed the same number of exercise sessions without targeted intensity. Cardiopulmonary exercise testing will be performed before and after the 8-week cardiac rehabilitation program to assess changes in cardiopulmonary function

**Table 3 Tab3:** A stratified randomization scheme based on gender

Male			Female		
Serial number	Random number	Group	Serial number	Random number	Group
1	0.699718	A	1	0.299478	A
2	0.474505	B	2	0.228082	A
3	0.278238	A	3	0.905825	B
4	0.063581	B	4	0.288985	B
5	0.543526	A	5	0.204267	B
6	0.645542	A	6	0.004536	A
7	0.606382	A	7	0.876704	A
8	0.358782	A	8	0.765598	A
9	0.913533	B	9	0.989875	B
10	0.394207	B	10	0.735247	B
11	0.101518	A	11	0.968638	A
12	0.830019	B	12	0.975038	A
13	0.454501	B	13	0.355564	A
14	0.941391	B	14	0.730377	B
15	0.748873	B	15	0.087323	B
16	0.736089	B	16	0.318215	B
17	0.026114	A	17	0.794593	B
18	0.294124	A	18	0.322396	A
19	0.801002	A	19	0.180908	A
20	0.448855	B	20	0.552161	B

Microsoft Excel Rand is performed to generate random numbers between 0 and 1, last digit even number for group A (intervention) and odd for group B (control). Patients are then allocated to intervention and control groups chronologically

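### Blind analysis is not ensured as described: the labels A and B meant to mask the statistician are the article's own published allocation codes

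*Protocol article*

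**What the plan says.** The limitations paragraph of the Discussion admits that "outcome assessment of metabolism and clinical indicators (blood pressure, heart rate etc.) is not blinded" and defers assessor blinding to a later, larger trial. It then offers a counterweight: an outside statistician, invited to work to an analysis plan fixed in advance. On how that person is masked, it says that "the groups will be labeled A and B, to ensure that the data are analyzed blind".

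The Randomization section gives those letters a meaning. For one letter, "if the last digit is an even number the patient will be assigned to group A (intervention"; for the other, "if the last digit is an odd number the patient will be assigned to group B (control". The same section repeats the meaning when it gives the planned 20 participants per group. The footnote to Table 3 states the rule again, "last digit even number for group A (intervention) and odd for group B (control", and adds: "Patients are then allocated to intervention and control groups chronologically". Table 3 itself lists 20 male and 20 female allocations, each marked A or B.

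**The concern.** A group label masks an analyst only if the analyst cannot tell which arm it stands for. Here the label proposed as a mask is the allocation code, and its meaning is printed in the same article. A statistician who has read the Methods and receives data labelled A and B knows the arms from the outset.

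This is more than a detail left to the analysis plan. The article names a mechanism and says that it secures blind analysis; as written, the mechanism does not.

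What is at stake is the discretion that any analysis leaves: handling of outliers and missing values, choice of scale, and which of many comparisons to stress. With a target of about 30 completers, such choices can visibly move a between-group difference. A reader would also credit the trial with a protection that the described procedure does not deliver.

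**Working it through.** No power or sample size figure is involved. The check compares statements, with a count on Table 3.

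**1. The letters in each place**

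| Place in the article | Role of A and B |
|---|---|
| Methods, Randomization | A is intervention, B is control |
| Methods, Table 3 footnote | A is intervention, B is control |
| Methods, Table 3 body | Every row carries A or B |
| Discussion, limitations | A and B are the labels that keep the analysis blind |

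The first three rows give the key to the fourth. Nowhere does the article say that the letters are reassigned before the data reach the statistician.

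**2. Does Table 3 use the letters consistently?** The rule is an even last digit for A and an odd one for B. Applied to the printed random numbers:

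- Male: 20 rows, 10 A and 10 B, no mismatches.
- Female: 20 rows, 10 A and 10 B, no mismatches.
- Total: 10 + 10 = 20 A and 10 + 10 = 20 B, so 40 of 40 rows follow the rule.

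Each letter therefore corresponds to exactly one arm.

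**3. Is there other blinding to fall back on?** Assessment of metabolism and clinical indicators is openly unblinded. No masking of participants, treating staff or laboratory is stated. The A/B labelling is the only blinding the article claims.

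**4. Which results depend on the labels?**

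- The feasibility criteria in Data assessment (40 recruited, 75% retention, all outcomes measured in 90% of participants) are stated for the trial as a whole. For example, 75% of 40 is 0.75 × 40 = 30, whichever arm those 30 come from. Arm labels do not enter.
- Between-group differences in mean change, with 95% confidence intervals, do depend on the arm. They cover the secondary outcomes and the exploratory biomarkers. Outcome measurements names 17 of the latter if interleukins count as one: 6 inflammatory, 1 immune-modulatory, 2 myocyte stress, 1 left ventricular, 1 oxidative stress, 1 hormone, 4 matrix remodelling and 1 signalling (6 + 1 + 2 + 1 + 1 + 1 + 4 + 1 = 17).

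**5. Would new letters alone be enough?** Because the footnote says that the list is used in order, a record's sex and serial number would point to its row in Table 3, whatever letter it carried. One caution applies. Trial status reports 6 intervention and 7 control among the first 13 patients. Taking the first k male rows and the first 13 − k female rows of Table 3, for k from 0 to 13, gives between 7 and 9 A and never 6. The list in use may therefore differ from the printed one. This route is possible rather than certain, but withholding the order costs nothing.

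**The case against.** The strongest reply is that publishing a key does not prove that the analyst holds it. The statistician is described as outside the study and working to a pre-specified plan that is not shown, and that plan may provide for recoding. A reader might infer that blinding is wholly absent and that every record is unmasked. The article does not support that: it would require that the statistician knows the key and receives the letters unchanged, and neither is stated. What stands is narrower. The only mechanism described does not secure what is claimed for it.

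A reader might also infer that attendance, session heart rate and activity-tracker records give the arms away. The article does describe heart-rate monitoring during intervention sessions and activity tracking for controls. However, Data collection and Outcome measurements list neither of these, nor attendance. The heart rate listed there is a clinical indicator taken from all participants before and after training. Nothing says that session or tracker fields would go to the statistician, so they matter only if they would otherwise be included.

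Finally, the consequence is limited. An independent analyst and a pre-specified plan both restrict discretion and do not rely on the labels. The planned analysis is descriptive, the biomarkers are exploratory, and the authors already warn that unblinded assessment may make the quantitative results unreliable. Masking the analyst could not repair that. These points reduce the size of the problem but do not reconcile the two statements.

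**Conclusion.** The point holds in limited form. The article says that labels A and B make the analysis blind, yet publishes what they mean, so blind analysis is not ensured as described. Every printed allocation (40 of 40) follows the published meaning.

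The exposure is confined to the between-group secondary and exploratory comparisons. A reader might infer that the primary outcome is compromised; it is not, because the feasibility criteria are overall figures. The document gives no basis for putting a number on any resulting bias.

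Two assumptions underlie the practical importance: that the statistician has access to the protocol, which is likely for someone working to a plan built on it, and that the letters are passed on unchanged, since no recoding is described. If either fails, the analyst may in fact be blind, but not by the means the article gives. The correction is worth making because it is nearly free and can still be made: 13 patients were enrolled at submission, and the assessment is planned for the end of the trial.

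**What to change.** Before data transfer, someone outside the analysis should recode the arms to two neutral codes unrelated to A and B, assigned at random so that their order carries no meaning. That person should hold the key until the between-group tables are final.

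The masked dataset should omit the Table 3 serial number and anything that reveals enrolment order. If arm-specific session or tracker fields would otherwise be included, they should be left out as well.

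The Discussion sentence should then describe this procedure. If it is not adopted, the statement that the data are analysed blind should be deleted; the outside statistician and the pre-specified plan can still be cited, since neither depends on masking.

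The cost is one recoding step and a sentence or so of text. Sample size, visits, measurements and the planned comparisons do not change.
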